#### 2.3.2 Physical activity

Physical activity will be measured with ActiGraph accelerometers (Actigraph, Pensacola, FL, USA) secured by a hospital band on participants’ non-dominant wrists for one full week (i.e., 5 weekdays and 2 weekend days). The devices will be placed on the child during the school day and set to start recording at midnight. The devices will be removed after seven full days of recording. The devices will be calibrated to collect data at 30 hz, the standard frequency used with accelerometers. Data will be reduced using Actilife software and physical activity behaviors will be determined using cut-points by Johansson et al [72]. The final outcome will be minutes of total and MVPA across the whole day and school day. To be included in the overall physical activity outcome, children will need 3 weekdays + 1 weekend with at least 10 hours of valid wear time[73, 74].

#### 2.3.3 Teacher perceptions

To determine teachers’ perceptions of MAP, we will ask them to complete two surveys- before the intervention (baseline; 7-question survey) and after the intervention (posttest, 9-question survey). Surveys were created for this project but were modeled after previous research studies that examined preschool teachers’ perceptions and experience with classroom-based interventions [75]. Surveys will ask how teachers perceive the following: (1) the importance of the program (n = 2 questions), (2) the ability of the program to help them address their goals regarding child gross motor and physical development (n = 1 question), (3) the appropriateness of the content (n = 2 questions), and (4) the ease of use of the program content (n = 2 questions). The post-test assessment also asks teachers two questions about their beliefs regarding the future use of the program.

#### 2.3.4 Teacher facilitation

We will send teachers a daily, 8-question survey asking about their facilitation of the program (see S1 File). We will also ask teachers to take daily photos of the motor skill activities on the provided tablet. This survey plus pictures is a proxy for intervention fidelity. Questions were designed to include 11 of the 12 TiDIER structures[76, 77]. Specifically, the survey includes information on the name of the program, materials, procedures, provider, mode of delivery, where/location, when/how much, tailoring, modifications, planned activities, and actual activities [76, 77]. Primary outcomes of interest will be teacher-reported facilitation as assessed as a percent of sessions and session components fully and correctly executed.

#### 2.3.5. e:Health platform feasibility, usability, and engagement

Feasbility and usability of the private YouTube channel will be assessed using the System Usability Scale [78–80]. Teachers in e:MAP classrooms will be asked to complete this survey three times: before the start of the program, one week after the start of e:MAP, and at the end of e:MAP. Engagement with the platform will be collected as the number of video views on e:MAP sessions weekly starting at the beginning of the intervention.

### 2.4 Timeline

This study will take place across the 2024–2025 school year. See Fig 1 for a full description of the study procedures and timeline.

**Fig 1 pone.0308047.g001:**
[figure not shown]
Study timeline and procedures.

### 2.5 Ethics approval

The Institutional Review Board at the University of Michigan has reviewed all study procedures. All study procedures involving collecting data from children have been approved (HUM00242675), and all study procedures involving teachers have been deemed exempt (HUM00252364).

### 2.6 Study procedures

This study will take place at a single early childhood center in the Midwestern United States during the 2024–2025 school year. The center is federally subsidized and provides high-quality early childhood education to children from low socioeconomic backgrounds. The center has agreed to partner on this research project and was consulted on all aspects of the study. The center will receive half of the equipment and be granted continued access to the program after the cessation of the project.

Before the start of the 2024–2025 school year, the research staff will attend the teacher professional development and provide a 1 to 2-hour overview of the project and the e:MAP program. In this session, we will review the purpose of e:MAP, the components of e:MAP, how to access and use the e:health platform, teacher facilitation expectations, and the recruitment plan. We will address any questions teachers or school staff have regarding the project. We will also be on-site once a month during the intervention period to address any concerns or assist with any technical difficulties. If teachers are not completing at least three e:MAP sessions per week, a member of the research team will contact them to offer additional support.

All teachers of classrooms with children who are eligible to enroll in the study will complete an initial survey on their perception of the programs (August 2024). Recruitment will start in August (see recruitment strategies #1 & #2) and September (recruitment strategy #3). Baseline testing of children’s outcomes (FMS and PA) will be completed in October 2024. Classrooms will then be randomly assigned to a MAP condition or a standard of care condition. Classrooms assigned to e:MAP will complete the intervention from November 2024 –February 2025. During this time, teachers whose classrooms are randomly assigned to the e:MAP program will facilitate the program by playing a daily e:MAP session video on a tablet provided to the classroom and setting up motor skills stations using the provided equipment and instructions. These teachers will also complete a daily facilitation survey. We will then complete post-test child health outcomes and surveys on teachers’ perceptions of MAP in February–March 2025.

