**Methods:**

This pilot study uses a pretest/posttest randomized cluster control design. We will recruit at least 64 children (3.5–5 years of age) enrolled in a single early childhood education center. Children will be randomly assigned at the level of the classroom to an e:MAP group (n~30) or a control group (n~30). Children in classrooms assigned to e:MAP will complete an 8-week intervention. We will collect measures of child FMS and physical activity, and teacher’s perceptions of the program before (pretest) and after the intervention (posttest). FMS measures include process (Test of Gross Motor Development-3rd Edition) and product-oriented scores. Physical activity will be assessed using a 7-day accelerometer wear protocol. Teachers’ perceptions will be assessed through a brief survey. Lastly, we will collect data on teachers’ ability to facilitate e:MAP through a daily survey.

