## 2. Materials & methods

### 2.1. Sample

All children enrolled in preschool classrooms at a single Head Start/Great Start Preschool in Michigan will be recruited. Based on initial MAP work [45], we completed a sample size calculation using an alpha level of 0.05 and a desired power of 80% when comparing the two groups to detect an effect size of Cohen’s d = 0.8 [64]. This estimated effect size represents a meaningful change in children’s motor skills and is higher than meta-analytic reports of average effects sizes from motor interventions [18, 22]. The calculation yielded a minimum of 54 children needed (27 per group). To account for 20% lost to follow-up, we will recruit 32 children per group. We will try our best to minimize the loss of follow-up, and this extra recruitment will help us maintain statistical power with any unexpected smaller detectable group differences in the outcome. Due to the nature of research in a school setting, children will be randomized at the level of the classroom. We will recruit from a minimum of 6 classrooms.

To be enrolled, children must meet the following at the time of study enrollment: 3.5–5.0 years old, able to understand simple verbal instructions in English, and be physically capable of completing the motor skills assessment. Children who have a physical or intellectual impairment that would inhibit them from successfully completing the motor skill assessment will be excluded.

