### 2.8 Planned analyses

Whole-study and group-specific descriptive statistics, including frequencies and percentages of categorical variables, along with mean and standard deviation of continuous variables, will be computed to summarize the sample characteristics. Between-group comparisons will be conducted at baseline to evaluate the success of randomization using two-sample t-tests. The post-intervention trajectory of FMS and PA will be assessed for any group differences, and we will use multilevel linear mixed effect models or generalized linear mixed effect models to determine covariate-adjusted differences between the MAP group and control group after the intervention, controlling for the established influence of sex, age, and anthropometrics on child outcomes [10, 70, 71]. Besides the main effect of each variable, the interaction term between intervention and sex will also be evaluated to investigate whether the intervention had a differential effect for boys and girls.

In regard to teacher outcomes, we will use a dependent sample t-test to explore if there are changes in teachers’ perceptions of the program at posttest. Teacher’s ability to facilitate the program will be reported as a percentage of sessions where teachers correctly executed MAP.

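### With as few as six classrooms randomised after baseline testing, a moderate chance baseline difference is plausible, yet the outcome model does not name the baseline score and relies on t-tests to check balance

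*Protocol article*

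**What the plan says.** Section 2.1 of the protocol article makes the classroom the unit of randomisation ("children will be randomized at the level of the classroom") and gives a lower limit on their number: "We will recruit from a minimum of 6 classrooms". The abstract expects about 30 children per arm.

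Section 2.6 fixes the order of events. First, "Baseline testing of children’s outcomes (FMS and PA) will be completed in October 2024". Next, "Classrooms will then be randomly assigned to a MAP condition or a standard of care condition". It describes no stratification, matching or constraint. It does not call the allocation simple or unrestricted either.

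Section 2.8 deals with baseline balance in two ways:
- **A check:** "Between-group comparisons will be conducted at baseline to evaluate the success of randomization using two-sample t-tests".
- **A model:** "we will use multilevel linear mixed effect models or generalized linear mixed effect models to determine covariate-adjusted differences", "controlling for the established influence of sex, age, and anthropometrics on child outcomes". The baseline FMS or PA score is not in that list. The same sentence speaks of a post-intervention trajectory, which could mean that baseline enters as a repeated measure, but the contrast it defines is the difference between groups after the intervention.

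**The concern.** With three classrooms per arm, one classroom of unusually skilled or unskilled children can shift an arm's mean. If the outcome model does not contain the baseline score, the part of that shift that persists to post-test, beyond what sex, age and anthropometrics explain, stays in the estimated intervention effect. It can mimic an effect or hide one. Later repair with classroom-level covariates is hardly possible, because six classrooms in two arms leave about 6 − 2 = 4 between-classroom degrees of freedom. A child-level baseline covariate does not face that limit to the same degree.

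The planned check does not help. A significance test at baseline changes nothing in the estimate. When classrooms are randomised and children are tested as if independent, it also rejects too often under proper randomisation, so it can wrongly suggest that randomisation failed.

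**Working it through.** **Inputs from the article.** At least 6 classrooms (section 2.1); about 30 children per arm (abstract), hence 60/6 = 10 per classroom; recruitment target 64 (section 2.1) and cap 90 (section 2.1.1); design effect size d = 0.8 (section 2.1). **Assumed:** a 3:3 split, equal classroom sizes, and ICC 0.05, 0.10 or 0.20, since the article gives no ICC.

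**The plan's own figure.** The article states no figure for imbalance. Its sample size is close to reproducible: d = 0.8, two-sided alpha 0.05 and 80% power need 26 per group by t-test. The stated 27 gives 82% power. This is a calculation for independent children, and it serves here only to supply d = 0.8 as a yardstick.

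**Step 1: size of the chance difference.** In child-level SD units, a classroom mean of m = 10 children has variance ICC + (1 − ICC)/10. The difference between two arms of three classrooms has SD = √[(2/3) × that variance].

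| ICC | Variance of classroom mean | SD of difference | P(>0.3 SD) | P(>0.5 SD) |
|---|---|---|---|---|
| 0.05 | 0.05 + 0.095 = 0.145 | 0.311 | 33% | 11% |
| 0.10 | 0.10 + 0.090 = 0.190 | 0.356 | 40% | 16% |
| 0.20 | 0.20 + 0.080 = 0.280 | 0.432 | 49% | 25% |

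The probabilities are 2 × [1 − Φ(threshold/SD)]. For example, 0.3/0.311 = 0.965 gives 33%.

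**Step 2: sensitivity to enrolment.** With 90 children (15 per classroom) and ICC from 0.01 to 0.20, a difference above 0.5 SD occurs in 3% to 22% of trials. With 64 children it occurs in 6% to 24%. More than six classrooms would lower these risks.

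**Step 3: what could reach the estimate.** If r is the pre-post correlation remaining after the named covariates, a baseline gap g leaves about r × g in an estimate that omits the baseline score. The article gives no r. For g = 0.3 SD this lies between 0 (r = 0) and 0.3 SD (r = 1), so at most 0.3/0.8 = 38% of the design effect. At an assumed r = 0.5 it is 0.15 SD, or 19%.

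**Step 4: the t-test.** With 30 children per arm treated as independent, the standard error is √(2/30) = 0.258, and p < 0.05 needs a difference of about 1.96 × 0.258 = 0.506 SD. Set against the SDs in Step 1, this happens by chance in about 10%, 16% and 24% of properly randomised trials, not 5%.

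**Step 5: what balancing the allocation could gain.** Six classrooms have 20 equal splits. Drawing at random from the 10 best-balanced, by simulation:

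| ICC | P(>0.3 SD), any 3:3 split | Balanced on one score | Balanced on three uncorrelated variables |
|---|---|---|---|
| 0.05 | 33% | about 4% | about 17% |
| 0.10 | 40% | about 7% | about 23% |
| 0.20 | 49% | about 14% | about 34% |

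The gain is large for a single score and much smaller when three variables share the constraint.

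**The case against.** The other side has a good case on several points.

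- **Allocation method.** A reader might infer that classrooms are allocated without any restriction. The article does not say so. It is condensed, and the mechanics of allocation may be in a fuller document. Arms of about 30 each suggest that a roughly equal split is intended. This stands: one can say only that no balancing is stated.
- **Tests alone.** A reader might infer that the plan does nothing about imbalance beyond testing for it. That is not so, because section 2.8 adjusts for sex, age and anthropometrics in a multilevel model. The gap is specific to the baseline outcome score.
- **Size.** A reader might infer that a large imbalance is likely. The figures do not support this: above 0.5 SD the chance is at most about one in four at the assumed ICCs, and six classrooms is a minimum.
- **Trajectory.** With two time points and mixed models, baseline may be meant to enter as a repeated measure. This is possible. But the article states a contrast after the intervention with a covariate list that omits baseline, so the ambiguity needs settling.
- **Availability of scores.** Completing baseline testing is not the same as having scores. Section 2.3.1 has an expert code all TGMD-3 trials and section 2.3.2 needs accelerometer data reduction, while the intervention starts in November. Nothing shows that scored data exist at allocation, so balancing on them cannot be called free.
- **Validity.** Plain cluster randomisation is unbiased on average. This also stands. The issue is precision and the credibility of one realised allocation.

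None of this rescues the baseline t-tests or supplies the missing covariate.

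**Conclusion.** The point holds as a minor one about analysis and, optionally, design. With six classrooms of 10 split 3:3, a baseline difference above 0.3 SD has roughly a one-in-three to one-in-two chance (33% to 49% at ICC 0.05 to 0.20). Above 0.5 SD the chance is 11% to 25%. The sizes rest on assumed ICCs, equal classrooms and the minimum number of classrooms. They describe baseline differences. The resulting error in the effect estimate is smaller by the residual pre-post correlation, which the article does not give.

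Two things are fixed badly in section 2.8: the baseline outcome is not clearly in the model, and a significance test that cannot correct imbalance, and that ignores clustering if run on children, is used to judge randomisation. The article does not establish that the allocation is unrestricted, and balanced allocation is a refinement, not a requirement.

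**What to change.** **In section 2.8:**
1. Name each child's baseline value of the outcome as a covariate in the multilevel model, next to sex, age and anthropometrics: TGMD-3 total, product score, motor competence score, or PA minutes, as applicable. If a repeated-measures model is intended, say so and state how baseline enters.
2. Keep classroom as a random effect and state a small-sample degrees-of-freedom correction, such as Kenward-Roger or Satterthwaite.
3. Replace the baseline t-tests with descriptive summaries by group.

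This costs a few sentences and no new data. One consequence should be planned for: a child without a valid baseline value, most likely for accelerometry, drops out of a model that conditions on it unless missing values are handled.

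**In section 2.6:** state how classrooms are allocated. If TGMD-3 coding will be finished before allocation, the team may list the equal splits (20 for six classrooms), rank them by the difference in classroom mean baseline TGMD-3, and draw one at random from the better-balanced half. The costs are coding 13 skills for all enrolled children before November, and 10 possible allocations instead of 20. Adding further balancing variables reduces the gain, as shown above.

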### 2.7. Safety considerations and adverse events

This study does not pose any additional safety risks for children above what is already present in outdoor free play. However, should an issue arise, the school administration will report the event to the researchers using the Adverse Event Report Form (see S2 File). Researchers will report adverse events to the hosting IRB and follow IRB protocols. Adverse event forms include nine questions on (#1) the date of the event, (#2) a description of the event, (#3) the severity of the event [*mild; moderate; severe; life-threatening*], (#4) if the event was related to the study [*not related; unlikely related; possibly related; probably related; definitely related*], (#5–6) description of the action taken [*none; dose modification; medical intervention; hospitalization; intervention discontinued; other*], (#7) the outcome of the event [*resolved; recovered with minor sequelae; recovered with major sequelae; ongoing/continuing treatment; condition worsening; death; unknown*], (#8) if the adverse event was expected [*yes; no*], and (#9) if this was a serious event [*yes; no*]. If the event is categorized as a serious event, a second form will be completed (form link: https://www.nia.nih.gov/sites/default/files/adverse_events_form.pdf).

### 2.8 Planned analyses

Whole-study and group-specific descriptive statistics, including frequencies and percentages of categorical variables, along with mean and standard deviation of continuous variables, will be computed to summarize the sample characteristics. Between-group comparisons will be conducted at baseline to evaluate the success of randomization using two-sample t-tests. The post-intervention trajectory of FMS and PA will be assessed for any group differences, and we will use multilevel linear mixed effect models or generalized linear mixed effect models to determine covariate-adjusted differences between the MAP group and control group after the intervention, controlling for the established influence of sex, age, and anthropometrics on child outcomes [10, 70, 71]. Besides the main effect of each variable, the interaction term between intervention and sex will also be evaluated to investigate whether the intervention had a differential effect for boys and girls.

In regard to teacher outcomes, we will use a dependent sample t-test to explore if there are changes in teachers’ perceptions of the program at posttest. Teacher’s ability to facilitate the program will be reported as a percentage of sessions where teachers correctly executed MAP.

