### 2.1.1 Recruitment

Study recruitment will begin in August 2024 and be completed in three ways: (1) by teachers using approved scripts during school home visits, (2) by the research team during parent/school open house events, and (3) through materials distributed through backpacks during the first month of school. Students will be enrolled on a first-come, first-served basis. If we have recruited 90 children, recruitment will end, and no additional students will be enrolled.

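### Baseline t-tests meant to judge the randomisation take no account of classroom, the randomised unit, and could not answer that question even if they did

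*Protocol article*

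**What the plan says.** Section 2.8 (Planned analyses) begins with descriptive statistics for the whole sample and by group, then states: "Between-group comparisons will be conducted at baseline to evaluate the success of randomization using two-sample t-tests". The sentence names no unit of analysis and no allowance for classroom. The next sentence turns to the post-intervention comparison and specifies multilevel mixed models adjusted for sex, age and anthropometrics.

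The randomised unit is clear elsewhere. The abstract says "Children will be randomly assigned at the level of the classroom", and section 2.1 repeats that "children will be randomized at the level of the classroom" and adds "We will recruit from a minimum of 6 classrooms". Section 2.6 gives the order of events: "Baseline testing of children’s outcomes (FMS and PA) will be completed in October 2024. Classrooms will then be randomly assigned to a MAP condition". Baseline values are therefore fixed before any classroom is allocated.

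**The concern.** There are two separate faults.

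- **Unit.** An ordinary t-test on children assumes independent observations. Children in one classroom share a teacher and setting and are allocated together. If their baseline scores are correlated, the standard error is too small and the test rejects more often than 5% when nothing has gone wrong.
- **Question.** The test is given the job of judging the randomisation. If classrooms are allocated at random after baseline measurement, the null hypothesis is true by design and any difference is chance. The p-value then says nothing about whether the allocation was carried out properly, whatever standard error is used.

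At stake is what the trial report will say about its own validity. A significant result may be reported as doubt about a sound allocation. A non-significant one may be reported as proof of balance that it does not give.

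**Working it through.** **Inputs from the document**

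- Classrooms: at least 6 (section 2.1). An equal split of 3 per arm is an assumption.
- Children: "To account for 20% lost to follow-up, we will recruit 32 children per group", so 32/3 = 10.7 per classroom, taken as 11.
- Upper limit: "If we have recruited 90 children, recruitment will end, and no additional students will be enrolled", so 90/6 = 15 per classroom with six classrooms.
- Level: 5%, taken as two-sided. Section 2.1 gives 0.05 for the sample size but states no level for the baseline tests.
- ICC: not given. A range of 0.01 to 0.20 is assumed.

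**The plan's own figure.** No figure is attached to the baseline tests. The nearest is the sample size, computed "using an alpha level of 0.05 and a desired power of 80% when comparing the two groups" for d = 0.8. The normal formula gives 2 × (1.960 + 0.842)² / 0.8² = 24.5, so 25 per group. The t-based solution is 25.5, so 26. The stated 27 per group is close and has t-based power of 82%. The figure thus reproduces as a comparison of independent children, with no design effect.

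**Rejection rate under correct randomisation.** The variance of the difference between arms is inflated by DE = 1 + (m − 1) × ICC, where m is the number of children per classroom. A test that ignores this rejects with probability of about 2 × [1 − Φ(1.96/√DE)]. For m = 11 and ICC = 0.10: DE = 1 + 10 × 0.10 = 2.00, 1.96/√2.00 = 1.386, and the rate is 2 × (1 − 0.917) = 16.6%.

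The formula was checked by simulating null trials (100,000 per cell, total variance 1, equal classroom sizes, pooled t-test on children):

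| Design | ICC | DE | Formula | Simulated |
|---|---|---|---|---|
| 3 classrooms of 11 per arm | 0.01 | 1.10 | 6.2% | 6.1% |
| | 0.05 | 1.50 | 11.0% | 10.9% |
| | 0.10 | 2.00 | 16.6% | 17.0% |
| | 0.20 | 3.00 | 25.8% | 26.7% |
| 3 classrooms of 15 per arm (90-child cap) | 0.01 | 1.14 | 6.6% | 6.7% |
| | 0.05 | 1.70 | 13.3% | 13.3% |
| | 0.10 | 2.40 | 20.6% | 21.2% |
| | 0.20 | 3.80 | 31.5% | 33.0% |
| 5 classrooms of 6 per arm | 0.01 | 1.05 | 5.6% | 5.7% |
| | 0.05 | 1.25 | 8.0% | 7.9% |
| | 0.10 | 1.50 | 11.0% | 11.0% |
| | 0.20 | 2.00 | 16.6% | 17.1% |

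In the same simulations a t-test on classroom means rejected in 4.9% to 5.1% of trials in every cell, and the child-level test rejected in about 5% at ICC 0. The excess is therefore due to clustering.

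**What a non-significant result would mean.** With 32 children per arm, the child-level test reaches significance only when the observed difference exceeds about 2.0 × √(2/32) = 0.50 SD. At an assumed ICC of 0.10 (m = 10.7, DE = 1.97), the chance difference between arms has a standard deviation of √(2/32 × 1.97) = 0.35 SD. A gap of 0.4 SD, half the planned effect of 0.8, is thus unremarkable by chance and would pass the test.

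**The case against.** The strongest reply is that nothing in the plan depends on these tests, and this stands. Section 2.8 sets no rule for acting on a significant result, fixes the covariates in advance on the ground of their known influence, and analyses outcomes with multilevel models. A reader might infer that a sound randomisation will be declared a failure, or that false alarms will drive the choice of covariates. The document supports neither.

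Other limits also stand:

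- The unit of the t-test is inferred. The sentence follows the sample descriptives and mentions no classroom adjustment, so child level is the natural reading, but it is not stated. Tests on classroom means would hold their level, with only 4 degrees of freedom at six classrooms, and would still not answer the question asked.
- No ICC is given. At 0.01 the inflation is slight, and six classrooms is a minimum, so more classrooms would reduce it.
- A reader might compound the error over many baseline variables into a much larger chance of at least one false alarm. The document does not list the variables to be tested, and its motor scores and activity measures overlap, so a calculation assuming independence would overstate that chance.
- A reader might infer that t-tests will be applied to sex. The text does not say so; it describes categorical variables by frequencies and percentages.
- Chance imbalance does not bias a randomised comparison in expectation. It affects precision and the particular estimate obtained.

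None of this rescues the stated purpose of the tests.

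**Conclusion.** The point holds as a fault in the baseline reporting. As written, the tests ignore the randomised unit. If done on children, their error rate rises from 5% to between about 6% and 27% per variable with three classrooms of 11 per arm, and to between about 6% and 17% with five classrooms of six. These figures assume ICCs of 0.01 to 0.20, equal classroom sizes and a two-sided 5% level.

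The second fault needs no ICC: no baseline significance test, adjusted for classroom or not, can measure whether randomisation succeeded. The consequence is limited to a misleading statement in the trial report. The planned outcome analysis is not invalidated.

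**What to change.** - Delete the sentence on baseline t-tests in section 2.8.
- Report baseline means and standard deviations, or counts, by arm and by classroom, with standardised differences between arms and no p-values.
- Add the baseline value of each outcome to the covariates named for the outcome model (now sex, age and anthropometrics), whatever imbalance is observed. The plan speaks of a trajectory, which may imply that baseline enters the model, but it does not say so.
- If a baseline test is kept, make it account for classroom, by a mixed model or a comparison of classroom means, and do not describe it as a check on the randomisation.

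The cost is one deleted sentence and one added covariate per outcome model. The October baseline measurements are already planned, so no data collection, sample size or allocation procedure has to change, and nothing useful is lost with the tests.

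### Section 2.8 names neither classroom as a model level nor a small-sample method, although as few as six classrooms may be randomised, so uncorrected mixed-model tests can reject too often

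*Protocol article*

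**What the plan says.** Section 2.1 of the protocol article fixes the unit of randomisation and its minimum number: "children will be randomized at the level of the classroom. We will recruit from a minimum of 6 classrooms". No maximum number of classrooms is given; section 2.1.1 caps enrolment at 90 children.

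For the child outcomes (FMS and PA), section 2.8 states: "we will use multilevel linear mixed effect models or generalized linear mixed effect models to determine covariate-adjusted differences". The models adjust for sex, age and anthropometrics, and an intervention-by-sex interaction is added. The section does not name the levels, the random effects, the estimation method or the reference distribution. Section 3 confirms that there are two time points.

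The sample size in section 2.1 is set "to detect an effect size of Cohen’s d = 0.8", "using an alpha level of 0.05 and a desired power of 80"%, and gives 27 children per group. No ICC or design effect appears.

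**The concern.** When classrooms are randomised, the difference between arms is judged against the variation between classrooms. With three classrooms per arm that variation is estimated on about 6 − 2 = 4 degrees of freedom, however many children are measured. A mixed model with a classroom random intercept addresses the clustering, but its usual z or likelihood-ratio test treats the between-classroom variance as if it were well known. With six clusters it is not.

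The word *multilevel* does not settle which level is meant. Section 2.8 also speaks of a trajectory, and each child is measured twice, so the level could be repeated measures within child. Classroom would then drop out of the model. The sample size and the baseline t-tests do not mention classroom either, so one cannot presume that it is carried through.

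Correlation within classrooms is plausible from the protocol itself. In the e:MAP arm each classroom's teacher chooses the session and sets up the stations (2.2.3), and school-day activity is an outcome (2.3.2). Goal 1 is to determine effects on child outcomes, so a difference between classrooms could be reported as an effect of e:MAP.

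**Working it through.** **Inputs from the protocol.** Classroom randomisation, minimum 6 classrooms (2.1); alpha 0.05, power 80%, d = 0.8, 27 per group (2.1); at most 90 children (2.1.1), which is 90/6 = 15 per classroom at the floor. The analysed minimum of 54 gives 54/6 = 9 per classroom.

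**Assumptions.** Two-sided test; equal classroom sizes of 9 to 15; ICC from 0 to 0.20, because the protocol gives none.

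**1. The plan's own figure.** A two-sample comparison of individual children needs n = 2(1.960 + 0.842)²/0.8² = 24.5, so 25 per arm. The exact t-test needs 26 per arm (power 80.7%); 27 per arm gives 82.2%. The stated 27 is therefore close to a calculation for individually randomised children, with no allowance for clustering.

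**2. Classroom left out.** The variance of the arm contrast is understated by the design effect DE = 1 + (m − 1) × ICC. The approximate type I error is 2Φ(−1.96/√DE).
- m = 9, ICC 0.05: DE = 1.40, error 9.8%
- m = 9, ICC 0.20: DE = 2.60, error 22.4%
- m = 15, ICC 0.05: DE = 1.70, error 13.3%
- m = 15, ICC 0.20: DE = 3.80, error 31.5%

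Simulation agrees closely (table below).

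**3. Classroom included, test uncorrected.** If between-classroom variance dominates, the statistic follows t with 4 df. Testing it at 1.96 gives P(|t₄| > 1.96) = 12.2%. At smaller ICCs the error must be simulated. The table shows type I error in simulated null trials (40,000–60,000 per setting, 3 v 3 classrooms, no covariates). The range in each cell covers 9, 11 and 15 children per classroom.

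| Analysis | ICC 0.05 | ICC 0.10 | ICC 0.20 |
|---|---|---|---|
| Classroom omitted | 9.8–13.4% | 14.7–21.4% | 23.1–32.5% |
| ML random intercept, z | 9.2–10.7% | 12.0–14.4% | 15.2–16.9% |
| REML random intercept, z | 6.9–7.9% | 8.5–10.0% | 10.4–11.3% |
| REML, Satterthwaite-type df | 4.3–4.9% | 5.0–5.3% | 5.2–5.3% |
| Classroom means, t with 4 df | about 5% | about 5% | about 5% |

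At lower ICCs, REML with z gives 4.0–4.2% (ICC 0), 4.8–5.0% (0.01) and 5.4–5.9% (0.02).

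**4. Cross-checks.** A covariate-adjusted REML fit with z, 9 per classroom, gave 6.2% at ICC 0.05 and 7.3% at 0.10. It had 600 replicates, so the standard error is about √(0.07 × 0.93/600) = 1 percentage point. With more classrooms at ICC 0.10, REML with z gave 7.9% for 8 classrooms and 7.0% for 10.

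**5. Price of valid inference at six classrooms.** The critical value is 2.776 with 4 df against 1.960, a ratio of 1.42. For a t-test on classroom means with m = 9, the standard error is √[(2/3)(ICC + (1 − ICC)/9)]. Power at d = 0.8 is then about 60% at ICC 0, 47% at 0.05, 39% at 0.10 and 29% at 0.20.

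**The case against.** The strongest reply is that this is silence and not error. The protocol nowhere states a z test, ML estimation or the omission of classroom. The estimator and the degrees-of-freedom method are commonly left to an analysis plan, which is not shown here. In a design described as cluster randomised, *multilevel* most naturally means classroom, and if only the post-test is modelled, classroom is the only higher level described. Most of this stands. The degrees-of-freedom method alone would be no finding. What remains is that this document chooses the model class, leaves its essential level open and allows six clusters, while its sample size ignores clustering.

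Four stronger readings are tempting and are not supported:
- *The plan ignores classroom.* The text does not say so. The 10–33% figures describe one possible reading.
- *The 5% level is not held and every interval is too narrow.* REML with z is at or below about 5% when the ICC is 0.01 or less. Corrected degrees of freedom are not excluded and keep the error at roughly 3–5% over the whole ICC range.
- *Intervals should be 42% wider.* That holds only at exactly six classrooms and for the same standard error. At low ICC, REML often sets the classroom variance to zero, so the standard errors differ.
- *There are about six classrooms.* Six is a minimum. The inflation shrinks with more, although it is still 7–8% with 8 to 10 classrooms at ICC 0.10.

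**Conclusion.** The point holds as a gap to close, not as a demonstrated invalid analysis. Section 2.8 does not name the classroom level or any small-sample method for a design that may have three classrooms per arm. Uncorrected tests can then have a type I error of about 7–11% (REML, z) or 9–17% (ML, z), and 10–33% if classroom is omitted, with interval coverage correspondingly below 95%.

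These figures rest on an assumed ICC of 0.05 to 0.20, exactly six classrooms of equal size with 9 to 15 children, and a model without covariates. The small covariate-adjusted check gave somewhat lower values (6.2% and 7.3% at ICC 0.05 and 0.10). That section 2.8 leaves the level and the method open is certain from the text; the size of the consequence is conditional. The change should be made.

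**What to change.** State in section 2.8 that classroom is a level of the child-outcome models, and choose one of two analyses:

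1. A classroom random intercept fitted by REML, with Kenward-Roger or Satterthwaite degrees of freedom for the arm contrast.
2. A two-stage analysis: covariate-adjusted child residuals averaged by classroom, then a t-test with classrooms minus 2 degrees of freedom.

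Add that uncorrected z tests, including those from a generalised linear mixed model, will not be relied on.

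A permutation test depends on the final number of classrooms. Split 3:3 there are 20 allocations and the smallest two-sided p is 2/20 = 0.10, so 5% cannot be reached. Split 4:4 there are 70, and 2/70 = 0.029 can be.

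The change is wording only and touches no data collection. Its downside is wider intervals and lower power, as shown in step 5 of the working for six classrooms.
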